### Endpoints/Evaluation criteria

#### Primary endpoint

The primary endpoint is the short-term efficacy (response to treatment) after 8 weeks of stimulation. A subject will be classified as a responder when he/she has three or more spontaneous, complete bowel movements per week during the 8 weeks of the trial. The primary endpoint was chosen considering the last randomized trial on severe chronic constipation published in the New England Journal of Medicine [9].

#### Secondary endpoints

Efficacy will be assessed by the following endpoints:Long-term efficacy (response to treatment) at 1 (T5) and 6 months (T6).Constipation symptoms will be assessed using the Patient Assessment of Constipation Symptoms questionnaire (PAC-SYM) [10]. This questionnaire includes 12 constipation-related symptoms scored on three subscales: stool, abdominal or rectal symptoms. For the overall scale and for each subscale, scores can range from 0 (symptoms absent) through 4 (very severe symptoms).Colonic transit time will be measured according to the Bouchoucha technique [11]. With this technique, the subjects ingest ten markers for 6 days at regular times. A plain film of the abdomen is performed at the 7th day. The number of persistent markers is analyzed in each area of interest (colonic segment). The total and segmental transit time is calculated by multiplying the number of markers by segment by 2.4. A slow transit time is defined by a total transit time greater than 91.2 h for women and 76.8 h in men.Ano-rectal manometry will be realized according to each center’s usual procedure. The following parameters will be collected: resting pressure and increment in the voluntary contraction measured in mmHg, maximal rectal tolerable volume in ml and presence of an anismus.Self-perception of the subject will be assessed using a patient global assessment of efficacy of the treatment based on an analogical visual scale (AVS) from 0 (not satisfied at all) to 5 (completely satisfied).The patients’ quality of life will be assessed using the Patient Assessment of Constipation Quality of Life (PAC-QOL) questionnaire [12]. This self-reported questionnaire includes 28 items related to the effects of constipation on the daily life on four subscales: physical discomfort, psychosocial discomfort, worries and concerns, and satisfaction. For each item, scores can range from 0 through 4 with lower scores indicating a better quality of life.Tolerance will be analyzed from the side effects or unexpected effect such as pain (local, ventral or dorsal) or neurological symptom such as paresthesia, burning and shaking.

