**Methods/Design:**

Design: multicenter, prospective, randomized, placebo-controlled, double blind, two-parallel groups study. Setting: nine French adult gastroenterology centers. Inclusion criteria: adult patients with a history of chronic constipation refractory to medical treatment for at least 3 months. Treatment groups: (1) interferential-experimental group (effective stimulation); (2) placebo-control group (sham stimulation). Randomization: 1:1 allocation ratio. Evaluation times: inclusion (T0, randomization), baseline assessment (T1), start of stimulation (T2), intermediary assessment (T3, 4 weeks), end of stimulation (T4, 8 weeks), follow-up (T5 and T6, 1- and 6-month). Endpoints: (1) primary: short-term efficacy at T4 (treatment response defined as three or more spontaneous, complete bowel movements per week); (2) secondary: efficacy at T5 and T6, symptoms (Patient Assessment of Constipation Symptoms questionnaire), colonic transit time, anorectal manometry, patient satisfaction (analogical visual scale), patient QoL (Patient Assessment of Constipation Quality of Life Questionnaire), side/unexpected effects. Sample size: 200 individuals to obtain 80 % power to detect a 20 % difference in treatment response at T4 between the two groups (15 % of lost to follow-up patients expected).

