#### Randomization

Computer-generated randomized lists will be drawn up before the beginning of the study, using a permuted block design, under the responsibility of the clinical research unit (AP-HM). The randomization will be stratified by center (1:1 allocation ratio). The allocation sequences will be sequentially numbered. The pharmacist responsible for the medical device distribution in the participating centers will take care of the lists. Prior to the study period, the participant, the treating medical staff and the investigators will all be unaware of the allocation.

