#### Data analysis

The data will be analyzed using SPSS version 17.0 software. The patients found to be eligible but not included in the study will be described and compared with the included patients. The patients who present at least one of the following conditions will not be included in the final analysis: patients inappropriately included despite providing consent and patients who withdrew their consent. The full analysis population (including all subjects who will be randomized and will be at least evaluated at T2) will be used in the primary analysis, and the *per protocol* population (including all subjects who will be randomized and will not have major protocol deviations) will be used in the secondary analysis to assess the robustness of the results. No interim analysis is planned. The normality of these parameters will be estimated using frequency histograms and the Shapiro test. The baseline parameters will be compared between the two groups (‘control’ and ‘experimental’) using the chi^2^ test or Fisher’s exact test for categorical variables and Student’s *t* test for continuous variables.

The proportion of treatment response at 8 weeks (patients with three or more spontaneous, complete bowel movements per week) will be calculated for each group and compared using the chi^2^ test or Fisher’s exact test for categorical variables. The center effect will be tested. The same procedure will be performed for the long-term efficacy. PAC-SYM scores, colonic transit times, manometric parameters, self-perception efficacy on the AVS and PAC-QOL scores will be compared between the two groups using Student’s test for continuous variables if applicable (or using nonparametric tests and the Mann-Whitney test). Changes between each initial score and the score at T3, T4, T5 and T6 will be compared between the two groups, and the analysis of variance for repeated measurements will be performed to compare the changes in the scores over time between the two groups. Multivariate analysis using logistic regression models will be performed to determine variables potentially linked to treatment response. Variables relevant to the models will be selected based on their clinical significance and/or a threshold *p*-value ≤ 0.2 in the univariate analysis. The final models will estimate the odd ratios and 95 % confidence intervals. All of the tests will be two-tailed with a 5 % significance level.

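### Ano-rectal manometry follows each center's own procedure, with no common anismus criterion and no center term clearly covering its analysis: this costs power and can dilute the anismus comparison, but does not bias it toward a false effect

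*Protocol article*

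**What the plan says.** Under Secondary endpoints, the protocol article states that ano-rectal manometry "will be realized according to each center’s usual procedure". It then lists what is collected: "resting pressure and increment in the voluntary contraction measured in mmHg, maximal rectal tolerable volume in ml and presence of an anismus". Parameters and units are therefore common, but the technique is not, and no rule is given for calling anismus present. The same section holds colonic transit time to one named technique, with a marker schedule, a conversion factor and sex-specific cut-offs.

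The abstract places the trial in "nine French adult gastroenterology centers". The Randomization section stratifies by center with permuted blocks and 1:1 allocation. Table 2 schedules manometry at T1 and T4 only.

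Under Data analysis, manometric parameters are listed with PAC-SYM, transit time, the satisfaction scale and PAC-QOL, and "will be compared between the two groups using Student’s test for continuous variables if applicable", with nonparametric tests such as Mann-Whitney as the alternative. Two other sentences there might bear on manometry. One says that the center effect will be tested, but it directly follows the comparison of the primary response. The other compares changes from the initial score, but it speaks of scores at T3, T4, T5 and T6, and manometry is not done at three of those four visits.

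**The concern.** Leaving the method to the centers is a stated choice, not a detail omitted for brevity, and an analysis plan cannot harmonise readings that were taken differently. If the local methods give different readings, the pooled pressures and volumes carry between-center variation that has nothing to do with treatment, and the stated two-sample test leaves it in its error term. Anismus is more exposed: it is a yes/no call, and without a shared rule a patient could be positive in one center and negative in another.

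Manometry is a named secondary objective and the trial's direct test of anorectal function. The Discussion says that evacuation disorders are enrolled on purpose alongside slow transit. What is at stake is whether a weak or null manometry result would say something about the treatment or only about the measurement.

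**Working it through.** **The plan's own figure.** The article gives no power figure for manometry, only the sample size for the primary endpoint. With 15% against 35%, two-sided 5% and 80% power, n per arm = [1.96·√(2·0.25·0.75) + 0.842·√(0.15·0.85 + 0.35·0.65)]² / 0.20² = 73 after rounding up, or 83 with continuity correction. 83 × 1.15 = 95.5, which matches the stated 95 per group approximately. The point below does not touch this figure.

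**Inputs for manometry.** From the article: 200 patients and 15% loss, so 100 × 0.85 = 85 evaluable per arm; nine centers; stratification by center; two-sided 5%. Assumed: the share of total variance due to center method (ICC), for which the article gives nothing.

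**Pressures and volumes, unadjusted test at T4.** Take the effect that has 80% power under one common procedure: d = (1.96 + 0.842)·√(2/85) = 0.43 within-center SD. Constant center offsets are balanced across arms by the stratification, so the true standard error of the difference hardly changes. The test, however, estimates its standard error from the total SD, which is larger by 1/√(1−ICC). Hence

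power = 1 − Φ(1.96/√(1−ICC) − 2.80), and type I error = 2·[1 − Φ(1.96/√(1−ICC))].

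| ICC (assumed) | SD factor | Power | Type I error |
|---|---|---|---|
| 0 | 1.000 | 80% | 5.0% |
| 0.05 | 1.026 | 78.5% | 4.4% |
| 0.10 | 1.054 | 77% | 3.9% |
| 0.20 | 1.118 | 73% | 2.8% |
| 0.30 | 1.195 | 68% | 1.9% |
| 0.50 | 1.414 | 51% | 0.6% |

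**What adjustment recovers.** A simulation with nine centers of 19 patients (2,000 runs per setting, assumed T1–T4 correlation 0.6) gave the following.
- Center-adjusted T4 test: 79% to 81% power for ICC from 0 to 0.5.
- Change from T1: 87% to 88% at every ICC, because constant offsets cancel within the patient.
- With scale differences between centers added (log-SD 0.1 to 0.3, ICC 0.2): unadjusted 72% to 74%, center-adjusted 78% to 80%, change about 86% to 87%.

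The gain from change scores depends on the assumed correlation ρ. The within-center variance factor is 2(1−ρ) for change and 1−ρ² for adjustment on the T1 value. At ρ = 0.6 these are 0.80 and 0.64; at ρ = 0.3 they are 1.40 and 0.91. Adjusting for T1 is therefore the safer form.

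**Anismus.** If the rule in use has sensitivity Se and specificity Sp against a single reference criterion, equally in both arms, the observed rate is Se·p + (1−Sp)(1−p), and the observed difference is (Se + Sp − 1) times the true one.
- At 0.95 each the factor is 0.90; at 0.90 each, 0.80; at 0.85 each, 0.70, a 30% loss.
- Illustration with assumed true rates of 40% and 20%: at 0.85 each, the observed rates are 0.40·0.85 + 0.60·0.15 = 43% and 0.20·0.85 + 0.80·0.15 = 29%. With 85 per arm, approximate power, Φ(difference/SE − 1.96), falls from 83% to 48%.

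Adjustment for center does not restore the lost difference, because the individual calls are already made.

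**The case against.** The strongest defence is the stratified randomization. Each center's method is spread over both arms, so stable method differences largely cancel in the treatment contrast. This stands, and it rules out several stronger readings that a reader might infer.

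- That a real effect would be buried: at ICC 0.05 to 0.30 the loss is about 1.5 to 12 points of power. Only an ICC near 0.5 brings power to about one half.
- That the variance inflation 1/(1−ICC), which is 1.25 at 0.20 and 1.67 at 0.40, amounts to losing 20% to 40% of the patients: under stratification the offsets inflate the estimated error, not the true one. Center adjustment returns the power without any new patient.
- That a change of equipment between T1 and T4 would look like a treatment effect: the planned comparison is between groups, so a change within a center would be expected to reach both arms about equally. It would add noise.
- That manometry is the only measure bearing on evacuation disorder: PAC-SYM has stool and rectal subscales, and the primary endpoint counts complete bowel movements.

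It is also fair to say that the article does not report how far the nine methods differ, that center adjustment may be specified in documents not shown, and that a reader could apply the chi-square test, named elsewhere in the section for categorical variables, to anismus. The change analysis, if meant to include manometry, would remove constant offsets. The wording does not settle either of these last two points. None of this answers the explicit delegation of the procedure or supplies an anismus rule.

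**Conclusion.** The point holds as a limited one on a secondary endpoint. The article delegates the manometry procedure, states no anismus criterion, and names a pooled comparison without a center term that clearly applies. There is no bias toward a false effect: the unadjusted test is conservative, with a type I error of about 2% to 4% at ICC 0.05 to 0.30.

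For pressures and volumes, the cost is a fall from 80% power to between 78.5% and 68% over that range, almost all recoverable in the analysis. For anismus, the cost is attenuation of any difference, 10% to 30% for sensitivity and specificity between 0.95 and 0.85, and it cannot be recovered afterwards. Both ranges are assumptions. One shared criterion removes only the part of the misclassification that comes from centers using different rules. The primary endpoint and the sample size are unaffected.

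**What to change.** Analysis, at no cost:
- Compare T4 pressures and volumes with adjustment for the T1 value and center, and say explicitly that this covers manometry.
- Analyse anismus with a center-stratified or logistic method instead of Student or Mann-Whitney.

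Measurement, before the first patient:
- Write one criterion for anismus.
- Set a minimum common end point for maximal tolerable volume that existing equipment can meet.
- Require the same equipment and settings at T1 and T4 for each patient.

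The measurement part needs a short sheet for nine sites that already perform the test at both visits; it adds no visit, test or staff. The downside is that some centers must adapt routine steps for trial patients. Trial status gives the study as not yet recruiting at submission, so on the article's own account these changes could precede data collection.

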### Pharmaceutical aspects

Devices (both effective or sham) and electrodes will be labeled and numbered according to the randomization list and sent to the dispensing pharmacist of each investigating center under the responsibility of the Hospital Pharmacy of AP-HM. At the end of the study, devices will be returned to the hospital coordinating pharmacy of the sponsor.

### Statistical considerations

#### Sample size, power and statistical methods

The sample size was determined to obtain an 80 % power to detect a 20 % difference in treatment response at 8 weeks between the two groups (15 % in the control group). This difference based on previous reports [1, 3, 9] has been considered to be clinically significant. With the threshold for statistical significance set at a *p*-value of 0.05, assuming that a potential 15 % of patients will be lost to follow-up, these calculations showed that 190 patients are needed (95 per group). A total of 200 individuals will be included.

#### Data analysis

The data will be analyzed using SPSS version 17.0 software. The patients found to be eligible but not included in the study will be described and compared with the included patients. The patients who present at least one of the following conditions will not be included in the final analysis: patients inappropriately included despite providing consent and patients who withdrew their consent. The full analysis population (including all subjects who will be randomized and will be at least evaluated at T2) will be used in the primary analysis, and the *per protocol* population (including all subjects who will be randomized and will not have major protocol deviations) will be used in the secondary analysis to assess the robustness of the results. No interim analysis is planned. The normality of these parameters will be estimated using frequency histograms and the Shapiro test. The baseline parameters will be compared between the two groups (‘control’ and ‘experimental’) using the chi^2^ test or Fisher’s exact test for categorical variables and Student’s *t* test for continuous variables.

The proportion of treatment response at 8 weeks (patients with three or more spontaneous, complete bowel movements per week) will be calculated for each group and compared using the chi^2^ test or Fisher’s exact test for categorical variables. The center effect will be tested. The same procedure will be performed for the long-term efficacy. PAC-SYM scores, colonic transit times, manometric parameters, self-perception efficacy on the AVS and PAC-QOL scores will be compared between the two groups using Student’s test for continuous variables if applicable (or using nonparametric tests and the Mann-Whitney test). Changes between each initial score and the score at T3, T4, T5 and T6 will be compared between the two groups, and the analysis of variance for repeated measurements will be performed to compare the changes in the scores over time between the two groups. Multivariate analysis using logistic regression models will be performed to determine variables potentially linked to treatment response. Variables relevant to the models will be selected based on their clinical significance and/or a threshold *p*-value ≤ 0.2 in the univariate analysis. The final models will estimate the odd ratios and 95 % confidence intervals. All of the tests will be two-tailed with a 5 % significance level.

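### Randomization is stratified by center, but the primary comparison is not: the test stays valid and adequately powered, yet turns conservative if centers differ strongly

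*Protocol article*

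**What the plan says.** - Randomization: permuted blocks, and "The randomization will be stratified by center (1:1 allocation ratio"). The abstract gives nine centers.
- Data analysis, primary endpoint: the proportions of responders at 8 weeks "will be calculated for each group and compared using the chi^2^ test" or Fisher's exact test. The next sentence is "The center effect will be tested", with no model named and no consequence for the treatment comparison. Long-term efficacy (T5, T6) follows the same procedure.
- Data analysis, regression: logistic models are planned to look for variables linked to response. "Variables relevant to the models will be selected based on their clinical significance and/or a threshold" univariate p-value of 0.2 or less.
- Screening and inclusion: a 2-week diary before treatment records weekly spontaneous, complete bowel movements (SCBM), the count on which the response definition rests. It is not named as a covariate for the treatment comparison.

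**The concern.** Stratified blocks force the arms to be nearly balanced within each center, so differences between centers contribute almost nothing to the true sampling variation of the treatment difference. An unstratified chi-square still counts those differences in its standard error. If centers differ in response rate, that standard error is too large, the test rejects too seldom under the null hypothesis, and some power is lost. A separate test of the center effect does not correct this, because it leaves the primary p-value as it was. With about 200/9 ≈ 22 patients per center, a non-significant result would also say little about whether centers differ.

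At stake are efficiency and agreement between design and analysis, at T4 and again at T5 and T6.

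**Working it through.** **Inputs from the protocol.** "All of the tests will be two-tailed with a 5 % significance level"; "The sample size was determined to obtain an 80 % power to detect a 20 % difference in treatment response"; control response "15 % in the control group", hence 35% in the experimental group; "assuming that a potential 15 % of patients will be lost to follow-up"; 95 per group needed, 200 to be enrolled; nine centers.

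**Step 1: the plan's own sample size.** With the pooled-variance formula, n = [1.96·√(2·0.25·0.75) + 0.842·√(0.15·0.85 + 0.35·0.65)]² / 0.20² = 72.4, so 73 per arm, and 73/0.85 ≈ 86. The arcsine formula with continuity correction gives 80.5, and 80.5/0.85 = 94.8. Fisher's exact test needs 81 per arm (80.2% power), and 81/0.85 = 95.3. The stated 95 per group is therefore reproduced.

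**Step 2: power of the planned test.** Enrolling 200 with 15% loss leaves 170, or 85 per arm. Power = Φ{[0.20 − 1.96·√(0.375/85)] / √(0.355/85)} = Φ{(0.200 − 0.130)/0.0646} = Φ(1.08) = 86%. Fisher's exact test has about 83%. Both exceed 80%.

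**Step 3: effect of leaving center out.** Let R be the within-center share of the outcome variance. With exact balance inside centers, the actual two-sided error of the unstratified test is about 2·[1 − Φ(1.96/√R)]. The protocol gives no figure for center differences, so a normal spread of center logits around a 15% mean response is assumed. Integrating numerically:

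| Assumed center SD (logit) | R | Approximate type I error |
|---|---|---|
| 0 | 1.00 | 5.0% |
| 0.5 | 0.97 | 4.6% |
| 1.0 | 0.88 | 3.7% |
| 1.5 | 0.78 | 2.6% |

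This is the limit under perfect balance. Incomplete blocks and dropout soften it, as simulation shows (200 patients, nine equal centers, blocks of 4 assumed because the protocol gives no block size, 15% random loss):

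| Center SD | Type I error, chi-square | Type I error, CMH | Power, chi-square | Power, CMH |
|---|---|---|---|---|
| 0 | 5.0% | about 5% | 87% | 86% |
| 0.5 | 4.8% | about 5% | 87% | 87% |
| 1.0 | 3.9% | about 5% | 87% | 90% |
| 1.5 | 3.1–3.5% | about 5% | 88% | 93% |

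To read the scale: logit(0.15) = −1.73, so centers one SD either side of a 15% rate run from about 10% to 23% at SD 0.5, 6% to 32% at SD 1.0, and 4% to 44% at SD 1.5.

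**Step 4: how much adjustment the data can carry.** Expected responders are 0.15·85 + 0.35·85 = 42.5. A logistic model with treatment, baseline count and nine fixed centers has 1 + 1 + 8 = 10 parameters besides the intercept, or 42.5/10 ≈ 4 responders each. In null simulations at 15% response, the likelihood-ratio test from that model rejected 5.7–6.6% of the time, against 4.8–5.3% for CMH. At center SD 0.5, 29–51% of simulated trials had a center with no responders.

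**Step 5: baseline count.** Its prognostic strength is not in the protocol. For assumed log-odds of 0, 0.5 and 1.0 per SD, with no center differences, a logistic model with treatment and baseline only had power of 85.5%, 88.1% and 90.1%, against 86.6%, 86.9% and 85.8% for the chi-square. That is a change of about −1 to +4 points (simulation error about ±1.2 points).

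**The case against.** The strongest defence has three parts.

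- **The loss is small and conditional.** At center SD up to 0.5 the planned test is as well calibrated and as powerful as CMH. An error rate near 3% needs center response rates spread roughly from 4% to 44%, and nothing in the protocol suggests this. This stands, and it limits the importance of the point.
- **Center is not ignored.** A test of the center effect is announced, and its details may properly sit in an SAP that is not shown. The second half is fair, and the missing detail is not the criticism here. But the protocol does fix the primary test, that test is unstratified, and a side test of center does not alter it.
- **Adjustment has a price.** With about 42 responders, a logistic model with nine fixed centers exchanges conservatism for mild inflation. This stands, and it is why that model is not recommended as primary.

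A reader might go further than the protocol allows:

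- *That the primary test gives too many false positives or is generally miscalibrated.* Its error is at or below 5% apart from simulation noise, and clearly below only when centers differ strongly.
- *That the trial is underpowered.* Step 2 shows otherwise under its own assumptions.
- *That baseline adjustment would bring a large gain.* Patients entering on the frequency criterion have two or fewer SCBM per week, which narrows the covariate. Others may enter on straining or incomplete evacuation. The mix and the prognostic strength are unknown.
- *That the 0.2 screening threshold damages the primary result.* The regression is presented as a search for predictors and does not feed the primary p-value.

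**Conclusion.** The point holds as one of efficiency and of matching the analysis to the design; it is not an error of validity. The primary comparison, and its repeats at T5 and T6, leave out the factor by which patients are randomized. Under assumed center SDs of 0 to 1.5 on the logit scale, the type I error of the planned test falls from about 5% to about 3%, and a center-stratified test changes power by about 0 to 5 points. The planned test exceeds 80% power throughout. These figures rest on 15% versus 35% response, 15% random loss, nine equal centers and an assumed block size of 4. The center spread is assumed and cannot be read from the protocol.

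**What to change.** 1. Make a CMH test stratified by center the primary analysis at T4, with a center-stratified risk difference and its 95% CI. Use the same at T5 and T6. A center with no responders adds nothing to the CMH statistic or its variance, so sparse centers do not break the test.
2. Keep the unstratified chi-square as a sensitivity analysis.
3. Pre-specify one supportive analysis adjusted for the baseline weekly SCBM count from the pre-treatment diary, without nine fixed center effects. Claim no particular gain for it.
4. Label the logistic predictor search exploratory, and state that the treatment effect will not be taken from it.

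The cost is wording in the protocol or SAP. Center and the baseline diary are already recorded, and no visits, data or patients are added. Trial status says recruitment had not begun at submission; made at that stage, the change would be fully pre-specified.

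### The continuous secondary endpoints are compared without baseline as a covariate, which is valid with complete data but wastes precision, and for PAC-SYM and PAC-QOL the named repeated-measures method normally drops patients who miss a visit

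*Protocol article*

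**What the plan says.** The Data analysis section of the protocol article gives three layers of comparison for the continuous secondary endpoints.

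- Values of PAC-SYM, colonic transit, manometry, the satisfaction scale and PAC-QOL are compared by t test or, where that is unsuitable, Mann-Whitney.
- For scores, "Changes between each initial score and the score at T3, T4, T5 and T6 will be compared between the two groups".
- Then "the analysis of variance for repeated measurements will be performed to compare the changes in the scores over time between the two groups".

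The only multivariable model in the section is a logistic regression for treatment response. No baseline covariate is named for any continuous endpoint. Testing of the center effect is mentioned once, directly after the responder comparison. On manometry, the Secondary endpoints section says "Ano-rectal manometry will be realized according to each center", the sentence continuing that the center's own customary method applies.

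Table 2 shows what is available. PAC-SYM and PAC-QOL are collected at T1, T2, T3, T4, T5 and T6. Transit and manometry are collected at T1 and T4 only. The article does not say whether the initial score is T1 or T2, or whether the T2 questionnaire precedes the first stimulation.

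**The concern.** In a randomized comparison, a follow-up score is partly predictable from the same patient's baseline. A raw follow-up comparison ignores that information. A change score uses it with a fixed weight of 1, which is usually too large, so the noise of the baseline measurement enters the estimate. ANCOVA estimates the weight from the data and also corrects chance baseline imbalance. The plan will compare the groups at baseline, but it does not carry the baseline values into these analyses.

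The second issue concerns only the questionnaires measured repeatedly. Classical repeated-measures ANOVA needs a complete row per patient, so one missed visit removes all of that patient's data. The trial expects losses: the sample size is set "assuming that a potential 15 % of patients will be lost to follow-up".

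At stake are the width of the confidence intervals and the power for symptoms, quality of life, transit and manometry. The primary responder analysis is not touched.

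**Working it through.** **The plan's own figure.** The only planned number is 190 patients (95 per group), with 200 to be included, for the responder endpoint. With 15% vs 35% response, two-sided 5% and 80% power, the usual formula gives 73 per arm, or 83 with continuity correction. 83 × 1.15 = 95.5, so the stated 95 is reproduced closely. It says nothing about the continuous endpoints, for which the article gives no SD, effect or power.

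**Inputs.**
- From the article: 200 patients and 15% loss, so 200 × 0.85 = 170 evaluable, or 85 per arm; and "All of the tests will be two-tailed with a 5 % significance level".
- Assumed: equal SDs at baseline and follow-up; r from 0.3 to 0.8; 3% to 10% of patients missing each post-baseline visit, independently.

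**Precision.** In large samples the variance of the treatment difference, in units of 2·SD²/n, is:
- raw follow-up: 1
- change score: 2(1 − r)
- ANCOVA: 1 − r²

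Hence change/ANCOVA = 2/(1 + r) and raw/ANCOVA = 1/(1 − r²).

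| r | Change | ANCOVA | Change/ANCOVA | Raw/ANCOVA | 170 patients by change score are worth, under ANCOVA |
|---|---|---|---|---|---|
| 0.3 | 1.40 | 0.91 | 1.54 | 1.10 | about 111 |
| 0.5 | 1.00 | 0.75 | 1.33 | 1.33 | about 128 |
| 0.7 | 0.60 | 0.51 | 1.18 | 1.96 | about 145 |
| 0.8 | 0.40 | 0.36 | 1.11 | 2.78 | 153 |

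A simulation of 5,000 trials with 85 per arm agrees. Change/ANCOVA was 1.58, 1.32 and 1.18, and raw/ANCOVA 1.10, 1.31 and 1.98, at r = 0.3, 0.5 and 0.7.

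The direction does not need equal SDs. With baseline SD s0 and follow-up SD s1, the change-score variance minus the ANCOVA variance is (s0² + s1² − 2r·s0·s1) − s1²(1 − r²) = (s0 − r·s1)², which is never negative.

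**Power.** Take a difference of 0.43 SD, which gives 80% power for raw follow-up with 85 per arm: (1.960 + 0.842) × √(2/85) = 0.43. Power for raw / change / ANCOVA is then 80 / 66 / 84% at r = 0.3, 80 / 80 / 90% at r = 0.5 and 80 / 95 / 98% at r = 0.7. Raw values beat change scores below r = 0.5 and lose above it. ANCOVA is the best of the three throughout, so r need not be known in advance.

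**Missed visits, PAC-SYM and PAC-QOL only.** If all four visits T3 to T6 are required, the fraction kept is (1 − m)⁴:
- m = 3%: 0.97⁴ = 0.885, so 11% dropped
- m = 5%: 0.95⁴ = 0.815, so 19% dropped
- m = 10%: 0.90⁴ = 0.656, so 34% dropped

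**The case against.** The strongest reply is that nothing here is an error. Randomization makes raw and change-score comparisons unbiased with complete data, their type I error is kept, and only secondary endpoints are involved. That stands: this is an improvement to a valid analysis. It does not make the point one for an unseen analysis plan, because the article names the methods itself.

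Four stronger readings are tempting, and the article does not support them.

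- *That transit and manometry are also analyzed by T3 to T6 change scores and repeated-measures ANOVA, and so lose anyone with a missed visit.* Table 2 schedules them at T1 and T4 only. The test clearly stated for them is the unadjusted comparison of values. The precision argument reaches them; the multi-visit argument does not.
- *That the plan prescribes complete-case deletion.* It gives the software but no procedure and no missing-data rule. Deletion is inferred from the named method. The separate change comparisons lose only patients without that visit or the baseline.
- *That repeated-measures ANOVA leaves about 69% of patients (0.85 × 0.95⁴).* This charges the method with the planned 15% loss, which is largely lost under any method: a mixed model recovers only visits made before dropout. The part due to complete-case analysis is 1 − 0.95⁴, about 19%, and it rests on the assumed 5%.
- *That center-specific manometry biases the comparison.* Randomization is stratified by center at 1:1, so the procedures are balanced between arms. What remains is extra variance of unknown size when center is left out.

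**Conclusion.** The point holds as a matter of efficiency. No continuous secondary endpoint is analyzed with its baseline as a covariate, although baselines exist for all of them except the satisfaction scale, which rates the treatment and has none. For r from 0.3 to 0.8 with equal SDs, change scores cost about 54% down to 11% extra variance against ANCOVA, and raw follow-up about 10% up to 178%. The direction is general; the size depends on an r that the article does not give.

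For PAC-SYM and PAC-QOL, a complete-case repeated-measures ANOVA would also drop about 11% to 34% of patients. This rests on an assumed 3% to 10% missed per visit and on the usual form of that method. A reader might infer that the results would be biased. That would need missingness related to outcome, which the article does not show. The change is worth making, but the primary conclusion does not depend on it.

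**What to change.** - **Transit and continuous manometric parameters:** ANCOVA of the T4 value on the T1 value, with treatment and center.
- **Anismus (present or absent):** logistic regression for T4 status, adjusted for T1 status, since ANCOVA does not suit a binary item.
- **PAC-SYM and PAC-QOL:** a mixed model for T3 to T6 with treatment, visit, treatment-by-visit, baseline and center, using all available visits. Report the adjusted T4 difference with its 95% confidence interval. Define the baseline as T1, or as the mean of T1 and T2 if the T2 questionnaire is completed before the first stimulation.
- **Rank tests:** keep as sensitivity analyses.

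This also settles which of the three stated analyses leads for each questionnaire score. The cost is a few lines of wording and slightly more analysis work. No new data are needed, and the article reports that recruitment had not started at submission.
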